
### Analyses

All statistical analyses will be conducted using the software package STATA version 15 (StataCorp, Texas). The data will be weighted to account for the multi-stage stratified cluster design and survey non-response. For the first two rounds of the survey weighting was done to account for the selection of catchment areas within districts, mother infant pairs within catchment areas and for survey non-response. For the final round survey, weighting is the same for the selection of clinics within districts, but differs for the later stage weighting. For this survey, weights will be constructed for the probability of being in a selected EA within the catchment area, the probability of complete census data within EAs (census non-response), and survey non-response among identified eligible mother infant pairs. GPS coordinates collected for each structure in selected EAs and will be used to assess whether census non-response is associated with distance from the clinic or distance from the center of the EA.

To assess the population-level impact of Option B+ (Objective 1), we will estimate and compare the population-level differences in MTCT and HIV-free infant survival among infants born after Option B+ is implemented (2017–18 estimates) and those born under the standard of care prior to Option A estimates (2012 estimates). Next, we will estimate the differences in these outcomes between infants born after Option B+ is implemented (2017–18 estimates) and those born under Option A guidelines (2014 estimates). These estimates will be generated by treating the two conditions compared in each analysis as matched pair observations for each catchment area, adjusting only for the sampling design through weighting. As with all pre-post evaluation designs, there is a concern that temporal trends, unrelated to the intervention, may be responsible for observed differences in the outcomes. To address this concern, we will also estimate differences in MTCT and HIV-free survival proportions adjusted for facility- and individual-level covariates not affected by the intervention. For example, in addition to demographic and socioeconomic characteristics such as the age of the mothers and infants, we will adjust for women’s ART use before pregnancy. To adjust for these factors, we will apply targeted maximum likelihood estimation, as well as standard parametric regression and inverse probability weighted methods.

To assess heterogeneity of the impact of Option B+ on HIV-free survival and MTCT among infants 9–18 months of age by the extent of integration of PMTCT and ART services at health facilities (Objective 2) we will first describe the variability in service integration, and characteristics of the facilities and catchment populations. We will capitalize on the variation of the integration score and other facility characteristics across the catchment areas to examine whether they affect the effectiveness of Option B+. We will describe differences in HIV-free survival by these facility-level characteristics. We will employ two identification strategies for these analyses. First, we will model 2017–18 outcomes adjusted for 2012 characteristics in each facility using ordinary least squares regression with HIV-free infant survival (or MTCT) as the aggregate continuous outcome. Similarly, we will model 2017–18 outcomes adjusted for 2014 characteristics. Second, we will apply a “difference-in-difference” approach, in which the outcomes will be defined as a) changes in HIV-free survival (or MTCT) between 2017 and 18 and 2012 in each catchment area, as well as b) changes in the same outcomes between 2017 and 18 and 2014.

Analysis for the retention of mothers in ART services after 19–36 months postpartum (Objective 3) will be primarily descriptive due to small sample size (e.g. 10% of eligible mothers 19–36 months postpartum). We will explore possible variations in the proportion of mothers who continued ART after weaning by whether the HIV-infected mother was or not on ART prior to PMTCT, to assess whether asymptomatic mothers were retained in care. We will also examine the average time between weaning and discontinuation of ART among those mothers who did not continue ART.

To determine the cost-effectiveness of the PMTCT program implementing Option B+ guidelines (Objective 4), we will estimate an incremental cost-effectiveness ratio (ICER). The ICER will be a ratio of the incremental cost of Option B+ over the incremental impact of a) the standard of care before Option A, and b) Option A. The costs will be expressed in monetary terms, and the benefits will be expressed in terms of HIV-free infant survival and MTCT rate. Detailed retrospective input and output data, as well as prices information will be collected from facilities We will estimate the facility-level annual economic costs of producing each modality of PMTCT services—prior A, A, B + —by adding the annual cost, i.e. monthly quantities multiplied by their prices, of three essential input categories used under each modality: personnel, ARV drugs and HIV tests kits. We will also estimate the average costs per woman enrolled in the PMTCT program, per facility, under each option. In 2012 and 2014 we collected data for standard of care pre-Option A and Option A, and in 2017–18 we will collect data for Option B+, for 1 year of implementation of each alternative retrospectively. Input data will include staff time devoted to the PMTCT programs, consumables such as HIV test kits and ART drugs. Unit prices and salaries for all these inputs will also be collected. Total costs for the different PMTCT models will then be estimated. For the same periods for which input data is collected, we will also gather data on the number women on each PMTCT alternative program, and will estimate the average cost per woman enrolled in PMTCT, per facility.

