Following the 2010 revision of the WHO PMTCT guidelines for resource-poor settings [7, 8] and the 2011 UNAIDS plan to eliminate MTCT globally [6], scale-up efforts for PMTCT interventions were renewed and highly efficacious ARV prophylaxis regimens became available in many low-income countries (e.g., Option A). Compared to earlier guidelines, Option A of the 2010 WHO guidelines recommended lifelong ART for a larger group of HIV-infected women (i.e., CD4 ≤ 350 or clinical stage 3–4 vs. CD4 ≤ 200), and that ARV prophylaxis be provided earlier in the pregnancy (i.e., starting at 14 weeks instead of 28) [9]. The commitment to scale up PMTCT interventions was further renewed in 2013 when the WHO released updated guidelines recommending that all pregnant women receive antiretroviral therapy throughout their lives regardless of clinical stage (Option B+) [10, 11]. However, MTCT rates in low resource settings remain higher than the levels achieved in efficacy studies [12, 13] or better-resourced settings, reflecting the reality that PMTCT effectiveness is a function of *both* ART efficacy *and* the proportion of HIV-infected pregnant women engaged and retained in PMTCT services [14]. In addition to accelerating the scale-up of PMTCT services, UNAIDS and WHO have urged countries to conduct population-level impact evaluations of their PMTCT programs [6, 15] to assess the extent to which these programs avert pediatric infections and to monitor progress towards PMTCT elimination goals [14, 15]. Despite the current global call for PMTCT effectiveness studies in developing countries, few countries have so far assessed the population-level impact of their PMTCT interventions [16, 17]. Equally unknown is the cost-effectiveness of PMTCT interventions such as Option B+, which remains a critical pending question in the context of limited resources for HIV programming.

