In Zimbabwe, eliminating MTCT poses a formidable public health challenge. An estimated 1.3 million people are living with HIV, with an estimated 4900 new HIV infections in children each year [18]. In 2011, Zimbabwe’s Ministry of Health and Child Care (MOHCC), intensified the existing PMTCT program and scaled up a nationwide program to accelerate the elimination of pediatric HIV/AIDS. Reaching 60 of 62 districts and approximately 1560 health facilities, MoHCC supported the implementation of Option A of the 2010 WHO guidelines, distributed point-of-care CD4 testing machines for determination of ART eligibility, and facilitated community mobilization to increase entry and retention in the PMTCT cascade. In November 2013, the MOHCC updated its guidance to Option B+ as recommended in the 2013 WHO guidelines.

The scale-up of the accelerated PMTCT program in Zimbabwe provides an opportunity to ascertain the effectiveness of PMTCT programs at a national level. We will combine three rounds of serial community-based cross-sectional serosurveys to evaluate the population-level impact of Option B+ in Zimbabwe. Our 2017–2018 endline serosurvey (post Option B+) will be combined with data from our previous serosurveys conducted in 2012 (pre-Option A standard of care) and 2014 (post-Option A/pre-Option B+). These three surveys will allow us to monitor population-level trends in MTCT and HIV-free infant survival over the previous 6 years and to assess the impact of Option B+ compared to i) pre Option A and ii) post Option A pre Option B+. We use a population-based approach, as estimates from facility-based studies by definition will be less likely to include women who do not attend clinics for antenatal care and delivery. As with many settings in sub-Saharan Africa, mobility and migration are also a concern in assessing outcomes as many women may move during the postpartum period and become lost or be considered lost to care from a facility when they change care locations. Our study design allows us to assess HIV-free infant survival and MTCT at a community level at 9–18 months postpartum, thus taking into account HIV transmissions occurring during pregnancy, labor and delivery and breastfeeding among both women who access PMTCT services and those that do not [17]. We will specifically collect information on antenatal care attendance and facility based delivery as well as changes in care location and gaps in care related to mobility/migration.

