## Methods/design

### Specific objectives

The specific objectives of this study include:Objective 1a, 1b: Compare the population-level impact of Option B+ on HIV-free survival and MTCT among infants 9–18 months of age in Zimbabwe to: a) standard of care before Option A; and b) Option A.Objective 2: Use facility and community level data to assess heterogeneity of the impact of Option B+ on HIV-free survival and MTCT among infants 9–18 months of age by the extent of integration of PMTCT and ART services at health facilities, among other factors.Objective 3: Assess retention of mothers in ART services 19–36 months postpartum.Objective 4a, 4b: Determine the cost-effectiveness of Option B+ compared to: a) the standard of care before Option A; and b) Option A.

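### The adjusted Objective 1 estimate treats ART use before pregnancy as unaffected by Option B+, although lifelong ART from an earlier Option B+ pregnancy partly produces it

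*Protocol article*

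**What the plan says.** Objective 1 is to "Compare the population-level impact of Option B+ on HIV-free survival and MTCT" with the standard of care before Option A (2012 round) and with Option A (2014 round).

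The Analyses section gives two kinds of estimate. The first is a matched-pair contrast by catchment area, "adjusting only for the sampling design through weighting". The second is added because "there is a concern that temporal trends, unrelated to the intervention, may be responsible for observed differences in the outcomes": differences will also be estimated "adjusted for facility- and individual-level covariates not affected by the intervention". Under that rule the section gives examples, among them "we will adjust for women’s ART use before pregnancy". Targeted maximum likelihood estimation (TMLE), parametric regression and inverse probability weighting (IPW) are to be used for this adjustment.

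The Background describes the 2013 WHO guidelines as "recommending that all pregnant women receive antiretroviral therapy throughout their lives regardless of clinical stage (Option B" and dates national adoption: "In November 2013, the MOHCC updated its guidance to Option B". Both quotes stop just before the plus sign; the option meant is B+. The Discussion makes the population benefit of Option B+ depend on mothers remaining in care for life.

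**The concern.** The rule for choosing covariates is sound, but the named covariate does not meet it for every woman. A mother who began ART in an earlier pregnancy under Option B+, and stayed on it as the programme intends, enters the index pregnancy on ART because of the programme. Her ART status before that pregnancy lies on the path from Option B+ to the infant's outcome.

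Objective 1 asks for population-level impact, which is a total effect. Conditioning on a variable on the causal path subtracts what passes through it. The three adjustment methods would share the same covariate and so the same bias, and agreement among them would be no reassurance. Because the adjusted estimate is the stated answer to temporal trends, any shrinkage from crude to adjusted would naturally be read as trend, when part of it may be programme effect.

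**Working it through.** The protocol article gives no figure on this point to reproduce. The check is a timeline, then the direction of the bias, then an illustration of size.

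**Timeline.** Inputs: adoption in November 2013 (Background); index infants born 9–18 months before the survey (Study site and population); rounds in 2014 and 2017–18. I assume that each round could fill its calendar years and that a pregnancy lasts 9 months.

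- 2017–18 round: births from January 2017 minus 18 months (July 2015) to December 2018 minus 9 months (March 2018). Conceptions run from October 2014 to June 2017, which is 11 to 43 months after adoption. An earlier Option B+ pregnancy is possible for part of the sample.
- 2014 round: births from July 2012 to March 2014, conceptions from October 2011 to June 2013. All precede adoption, as do those of the 2012 round.

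Option B+ can therefore raise the covariate in the 2017–18 round only. The article does not limit the covariate to ART started before November 2013 or outside PMTCT.

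**Direction.** Let a14 and a17 be the shares of HIV-infected mothers on ART before the index pregnancy, RR the risk ratio for infant infection or death (on versus not on ART before pregnancy, equal in both rounds), and f the fraction of the rise in that share due to Option B+. Write g(a) = (1 − a) + a × RR. Risks among mothers not on ART before pregnancy are r14 = 0.048 / g(a14) and r17 = 0.034 / g(a17). The 4.8% (2014) and 3.4% (2017–18 target) come from Statistical power. Assume that the fall within strata is wholly due to Option B+.

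- Without Option B+, the 2017–18 share would be a* = a14 + (1 − f)(a17 − a14). The true effect is r14 × g(a*) − 0.034.
- The adjusted difference, standardised to the 2017–18 mix, is (r14 − r17) × g(a17).
- Effect lost = r14 × (1 − RR) × f × (a17 − a14).

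The loss is positive whenever the share rose, ART before pregnancy lowers risk, and some of the rise came from Option B+.

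**Size (illustration only).** The shares, RR and f below are assumptions, not document figures. The adjusted difference here is standardised to the average of the two mixes. Middle case: shares 30% and 50%, RR 0.5.

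- r14 = 0.048 / 0.85 = 0.0565; r17 = 0.034 / 0.75 = 0.0453.
- Adjusted difference = (0.0565 − 0.0453) × 0.80 = 0.0089, or 0.89 points, against 1.40 crude.
- With f = 0.5, a* = 0.40 and the true effect is 0.0565 × 0.80 − 0.034 = 0.0112, or 1.12 points. Share removed = 1 − 0.89/1.12 = 20%.

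| Share on ART before pregnancy | RR | f | Adjusted (points) | True effect (points) | Removed |
|---|---|---|---|---|---|
| 30% to 40% | 0.75 | 0.25 | 1.29 | 1.30 | 1% |
| 30% to 50% | 0.5 | 0.25 | 0.89 | 0.98 | 9% |
| 30% to 50% | 0.5 | 0.5 | 0.89 | 1.12 | 20% |
| 30% to 50% | 0.5 | 1 | 0.89 | 1.40 | 36% |
| 30% to 60% | 0.25 | 1 | 0.01 | 1.40 | 99% |

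In the f = 0.5 row the crude-to-adjusted gap is 1.40 − 0.89 = 0.51 points. Of this, 1.40 − 1.12 = 0.28 is background trend rightly removed, and 1.12 − 0.89 = 0.23 is programme effect wrongly removed. The true value lies between the estimate without the covariate and the one with it.

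**The case against.** The strongest reply is that the covariate is there for a good reason. Women in a first pregnancy, and women who started ART through general care, carry exactly the background ART expansion that the plan wants to remove. The Background says that Option A also widened lifelong ART, and ART begun then is not an Option B+ effect in the 2014 comparison. Dropping the covariate could credit such expansion to Option B+, a bias in the opposite direction. This stands, and it is why the remedy is not simple removal.

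Second, the weighted matched-pair contrast comes first, is free of this problem, and is the comparison on which the sample size rests; the adjusted estimate is additional. This also stands and limits the consequence.

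Third, the mediated route needs an earlier pregnancy under Option B+, retention on ART, and a second conception within the window. The article's median breastfeeding duration of 17.8 months suggests spacing that limits how many women qualify. That is fair as to size, but it does not make the covariate unaffected.

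A reader might go further and infer that adjustment wipes out most of the Option B+ effect, or that this is a main route by which Option B+ works. The article gives no pre-pregnancy ART proportions, no risks by ART status and no repeat-pregnancy rates, so neither inference is supported. Nor does it say that the covariate-adjusted effect enters the cost-effectiveness ratio, so no consequence there can be claimed.

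**Conclusion.** The plan breaks its own covariate rule. Among women with an earlier Option B+ pregnancy, ART use before the index pregnancy is a product of the intervention; among others it is a confounder. Adjusting for all of it biases the adjusted Objective 1 estimate towards no effect, provided that pre-pregnancy ART rose between rounds and lowers infant risk. Only the direction is firm. The share of the effect removed ran from about 1% to 99% over shares rising from 30% to 40–60%, risk ratios of 0.25 to 0.75 and 25–100% of the rise due to Option B+, all assumed. In the 2012 comparison, ART started under Option A also feeds the covariate, which further blurs what the adjusted figure measures. The unadjusted contrast is sound on this point.

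**What to change.** - Stop describing ART use before pregnancy as a covariate unaffected by the intervention.
- Report the TMLE, regression and IPW estimates twice: without it (total effect, which may still contain background ART expansion) and with it (labelled as the effect not passing through pre-pregnancy ART).
- State that the gap between crude and adjusted results is not to be read as purely temporal trend.
- Where existing data allow, add a sensitivity analysis that counts only pre-pregnancy ART started before November 2013 or outside PMTCT. On the timeline above, the date-based version needs start dates from the 2017–18 round only, because all comparator conceptions precede adoption; it leaves in general-care ART started later. The version based on where ART was started needs that information from every round, and a new questionnaire item cannot supply it for 2012 and 2014.

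The cost is mainly wording and one extra run of each model. The downside is two adjusted estimates that bracket the effect, under the assumptions shown, instead of one.

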### Facility survey

In addition to the community-survey of mother infant pairs, surveyors will administer a questionnaire to the head nurse at each of the 157 health facilities in the selected catchment areas to assess the nature and integration of PMTCT and ART services offered at each facility and to collect information on other health facility characteristics. The survey also includes comprehensive resource utilization and cost information including: 1) the number and type of staff working in PMTCT, 2) PMTCT-related supplies used, 3) the monthly number of ANC and PMTCT clients in the previous calendar year, 4) the amount of staff time allocated to PMTCT services, and 5) the management practices implemented at the facility, such as supervision incentives. Facility records, such as staff rosters, supply stock records, and patient records will be used to corroborate self-reported information when available.

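### The Objective 4 cost sum leaves out CD4 testing, an input the protocol ties to ART eligibility under the comparators but not under Option B+, and so risks overstating the incremental cost of Option B+.

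*Protocol article*

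**What the plan says.** The Objective 4 paragraph of the Protocol article (Methods/design, Analyses) forms the annual facility cost of each modality by adding up monthly quantities times prices "of three essential input categories used under each modality: personnel, ARV drugs and HIV tests kits". The data-collection sentence later in that paragraph is looser: "Input data will include staff time devoted to the PMTCT programs, consumables such as HIV test kits and ART drugs". The Facility survey section is wider again: "The survey also includes comprehensive resource utilization and cost information including", followed by a list that names PMTCT supplies and monthly client numbers.

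On eligibility, the Background says Option A "recommended lifelong ART for a larger group of HIV-infected women" than before, defined as CD4 up to 350 or clinical stage 3–4, against a CD4 threshold of 200 under earlier guidelines. It says the Option A programme "distributed point-of-care CD4 testing machines for determination of ART eligibility". It describes Option B+ as lifelong treatment for all pregnant women, whatever their clinical stage.

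On the ratio, Study measures (secondary outcome 6) defines the ICER as a cost difference divided by a difference in effectiveness after annual adjustment. The Objective 4 paragraph puts the incremental cost of Option B+ "over the incremental impact of a) the standard of care before Option A, and b) Option A". It also mentions total costs for each model and says the team "will estimate the average cost per woman enrolled in PMTCT, per facility".

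**The concern.** An ICER depends only on differences between options. An input left out of every arm does no harm if it costs the same in each. CD4 testing is unlikely to be such an input, because the article's own account makes it part of deciding who starts ART under the comparators and gives it no such role under Option B+. A sum that excludes it removes cost mainly from the comparator side.

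Cost-effectiveness is a stated objective, and the Discussion offers the results to Zimbabwe and other developing countries. The costing rule is also not merely abbreviated: the article names the three categories to be added, and that list does not fit its own description of the programme being costed.

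**Working it through.** **Does CD4 testing fall inside the sum?** The categories are personnel, ARV drugs and HIV test kits. Staff time spent on CD4 testing may be captured under personnel. CD4 tests or cartridges and the machines are captured nowhere.

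**Does the omission cancel?** Setting the article's statements side by side:
- Earlier guideline: a CD4 threshold of 200 for lifelong ART.
- Option A: CD4 up to 350 or clinical stage 3–4, with point-of-care machines distributed for the purpose.
- Option B+: treatment irrespective of clinical stage, with no CD4 step described.

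The input is tied to eligibility in both comparators and not in Option B+, so there is no reason to expect it to cancel in either comparison.

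**How sensitive is the ICER?** The article states no cost, coverage or ICER figure, so there is nothing to reproduce. The effect differences come from the planning proportions for infant death or HIV infection in Statistical power: 10% (2012), 4.8% (2014) and 3.4% (2017–18 planning value).

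- Option B+ versus Option A: ΔE = 0.048 − 0.034 = 0.014
- Option B+ versus pre-Option A: ΔE = 0.10 − 0.034 = 0.066

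Let d be the omitted CD4 cost per HIV-exposed pair under the comparator minus that under Option B+. Then

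ICER as planned − ICER with CD4 included = d / ΔE.

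For d = 1 the shift is 1/0.014 = 71.4 units per additional HIV-free surviving infant against Option A, and 1/0.066 = 15.2 against pre-Option A. The values of d below are assumptions that show the range:

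| d (currency units per HIV-exposed pair) | Shift vs Option A | Shift vs pre-Option A |
|---|---|---|
| 5 | 357 | 76 |
| 10 | 714 | 152 |
| 20 | 1,429 | 303 |

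These shifts are before any annual adjustment of effectiveness and apply to HIV-free survival. The article gives no 2014 MTCT figure, so the corresponding shift for MTCT cannot be calculated.

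**Why the population basis needs fixing.** The effect is a proportion among all HIV-exposed infants in the community, whether or not their mothers used services. If a cost k per enrolled woman were used as it stands, it would differ from the cost per pair in the population, c × k, where c is coverage. With assumed costs of 100 and 150 per enrolled woman:
- Coverage 80% in both periods: (150 − 100)/0.014 = 3,571 per enrolled woman, against (0.80×150 − 0.80×100)/0.014 = 2,857 on the population basis.
- Coverage rising from 80% to 95%: 3,571 against (0.95×150 − 0.80×100)/0.014 = 62.5/0.014 = 4,464.

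The discrepancy can go either way, so the choice of basis matters.

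**The case against.** The strongest reply is that data collection is wider than the three categories. The facility survey covers PMTCT supplies, and the wording about consumables is open-ended, so CD4 costs may well be in hand. That stands, but it makes the omission easy to repair rather than harmless, because the costing rule as written sums only the three categories.

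It is also fair that clinical stage was an alternative route to ART under Option A, that the article does not say CD4 testing ceased under Option B+, and that staff time on CD4 testing may already be counted. All three reduce d and leave its size open. None gives a reason for it to be zero.

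Other omitted inputs, such as viral-load tests or infant PCR, could raise the cost of Option B+ and offset the CD4 effect. This stands, and it means the net direction across all omissions is not established.

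A reader might infer that the plan divides cost per enrolled woman by a population-level effect. The text does not say so. That average is introduced as an additional estimate, alongside facility annual costs and total costs, and is never named as the ICER numerator. A reader might also take the denominator phrase in Analyses as dividing by the comparators' own impact. Objective 4 and secondary outcome 6 make the intended comparison clear, so this is loose wording.

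**Conclusion.** The concern holds for CD4 consumables and equipment. The plan fixes a three-category cost sum that excludes an input its own Background ties to the comparators and not to Option B+. Taken alone, this understates comparator cost and risks overstating the incremental cost and ICER of Option B+ in both comparisons. It matters more against Option A, where the planned effect difference is only 1.4 points: about 71 ICER units per unit of net CD4 cost omitted, compared with about 15 against pre-Option A.

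These sensitivities assume the planning proportions are realised. A smaller observed difference would enlarge the shift, and a larger one would shrink it. No percentage bias can be given, because the article states neither the CD4 unit cost nor the incremental cost.

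A reader might go further and conclude that the Option B+ ICER is already wrong, or is biased against Option B+ overall. The document does not support that: no ICER has been reported in it, the survey may supply the missing data, and other omitted inputs may act in the opposite direction. The point concerns a secondary outcome and leaves the primary outcomes and the sample size untouched.

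**What to change.** 1. Extend the input sum in the Objective 4 paragraph, for all three modalities, to CD4 testing (tests or cartridges plus annualised machine cost) and any other laboratory test whose use differs between modalities. Draw quantities from the supplies item of the facility survey, and collect unit prices. If CD4 testing is to stay out, state the reason.
2. Where 2012 or 2014 quantities were not recorded, impute them as client counts times unit price and report a sensitivity range.
3. State that the ICER's incremental cost is expressed per HIV-exposed pair in the catchment population, the same basis as the effect. Keep cost per enrolled woman as a separate descriptive result.
4. Reword the ICER sentence in Analyses to match secondary outcome 6: the cost difference over the effectiveness difference between Option B+ and each comparator.

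The cost is a few wording changes and a few additional cost lines. The small downside is that imputed figures for the earlier rounds will be less certain than recorded ones, which the sensitivity range should show.
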